### Objectives

This RCT evaluates the effect of an individualized graded aerobic exercise intervention in adults with PPCSs from the general population. Participants undergo an intensive battery of physical and magnetic resonance imaging (MRI) examinations, alongside personal interviews and process evaluations, throughout the intervention period. The project is divided into the following 4 subprojects:

Subproject 1: This subproject aims to understand the challenges faced by patients with PPCSs, particularly their potential intolerance to physical activity and exercise, through qualitative in-depth interviews. It is hypothesized that the interviews will reveal significant obstacles to living a normal life, with a focus on intolerance to activity and exercise.Subproject 2: This subproject aims to evaluate the efficacy of a 12-week, heart rate–controlled aerobic exercise program for patients with PPCSs. It is hypothesized that the specialized exercise program will increase the physical capacity of patients, raising the threshold of symptom provocation compared with a group of controls.Subproject 3: This subproject aims to quantify the neurofunctional aspects of PPCSs using MRI for measuring changes in brain structure and function. It is hypothesized that patients with PPCSs will exhibit increased BBB permeability, disturbances in brain metabolism, and abnormalities in brain structure and physiology compared with a group of healthy age-matched controls. The exercise intervention is expected to normalize the physiological aspects of these MRI metrics in the training group (TG).Subproject 4: This subproject aims to obtain qualitative feedback from patients and researchers on various aspects of this interprofessional scientific project, utilizing a strengths, weaknesses, opportunities, and threats (SWOT) framework. Finally, we will conduct a comprehensive 360-degree evaluation that combines subjective and objective data to attain a novel understanding of the complexity of PPCSs.

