### Randomization and Blinding

Randomization to either the TG or the CG occurred after completion of the clinical screening examination and followed a 1:1 allocation ratio. Because PPCSs are more prevalent among women than men, an equal sex distribution was not anticipated; however, the allocation ensured an equal number of patients with PPCSs in each group. The randomization sequence was generated by [name], who was not involved in any other aspect of the trial, including patient recruitment, assessment, intervention delivery, data management, or analysis, thereby maintaining independence and minimizing the risk of allocation bias. The sequence was produced a priori using a computer-generated randomization list created through an online tool provided by Sealed Envelope. Allocation was implemented according to this pregenerated list, ensuring that those responsible for enrolling patients and assigning them to groups had no access to the randomization sequence prior to assignment, which is in line with SPIRIT recommendations for allocation concealment.

For all baseline assessments in subproject 2 (physiological evaluation), the tester was blinded to group allocation. The tester was also blinded to group allocation for all 12-week follow-up assessments. In addition, different testers conducted the baseline and 12-week follow-up assessments. Furthermore, the personal trainers supervising the exercise sessions were different from all the testers.

In subproject 3 (neurofunctional evaluation), which involved collecting and analyzing MRI data, a blinding protocol was strictly followed. The project staff handling and analyzing the MRI data were unaware of the participants’ group allocations. Similarly, the project leaders and statisticians were blinded to group allocations in the dataset used for the physiological and neurobiological analyses.

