$$\begin{array}{c} Y_{ij}=\beta_{0}+\beta_{1}{\text{Group}}_{i}+\beta_{2}{\text{SaO}}_{2,ij}+\beta_{3}({\text{Group}}_{i}\times {\text{SaO}}_{2,ij})\\ +\beta_{4}{\text{Age}}_{i}+\beta_{5}{\text{Sex}}_{i}+u_{i} \end{array}$$

where *Y*_*ij*_ denotes CMRO2, Group refers to either healthy controls or patients with PPCSs, and SaO2 is the actual oxygen saturation level in blood measured during the experiment (ie, during normoxia and hypoxia). Thus, we take the actual individual level of blood desaturation into account. The regression value *β*_3_ of the interaction term provides an inference regarding the patient’s ability to maintain CMRO2 under hypoxic stress conditions. After the 12-week intervention period, only patients will be tested for a possible change in their ability to maintain CMRO2 during the hypoxic exposure. Patients will be split according to group allocation (CG or TG), and the model is formulated as follows:

$$\begin{array}{c} Y_{ijk}=\beta_{0}+\beta_{1}{\text{Group}}_{i}+\beta_{2}{\text{SaO}}_{2,ijk}+\beta_{3}{\text{Time}}_{jk}\\ +\beta_{4}({\text{Group}}_{i}\times {\text{SaO}}_{2,ijk}\times {\text{Time}}_{jk})+\beta_{5}{\text{Age}}_{i}+\beta_{6}{\text{Sex}}_{i}+u_{i} \end{array}$$

where Time_ijk_ codes for pre- or postintervention (*k*) and Group codes for either the CG or TG, with the other parameters being as described above. The interaction term infers information on whether time (pre- or postintervention) has any impact on the group-specific CMRO2 response. Comparison of BBB permeability between patients with PPCSs and healthy controls will be performed using a linear regression model adjusted for age and sex, with heteroscedasticity-consistent SEs to account for possible nonconstant error variance. For exploratory regional analysis of BBB permeability across multiple brain parcels, Benjamini-Hochberg false discovery rate correction will be applied to control for multiple comparisons.

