## Discussion

We have presented the protocol for an RCT that evaluates the effect of an individualized physical aerobic graded exercise intervention in adults with PPCSs. The study has also used an intensive battery of physical and MRI-based examinations, as well as personal interviews and process evaluations. To our knowledge, this combined research methodology is scarce and could lead to a novel and integrated understanding of the complex phenomenon of persistent symptomatology and functional disabilities following PPCSs, where traumatology involves substantial neurological impairment. However, no single generally accepted pathophysiological component has been identified for this illness; rather, patients experience physical, neurological, cognitive, and perceptual inabilities. Combining an intervention study with an MRI-based investigation of brain physiology provides an opportunity to disclose the interaction between physical activity and brain function. While there is evidence for a beneficial effect of subsymptomatic exercise rehabilitation in patients with PPCSs [17,18], the impact on brain function is less known. Several MRI studies have pointed to microstructural abnormalities and possible changes in the brain functional connectivity network, using diffusion tensor MRI [49,50] and BOLD MRI [51,52]. Furthermore, autonomic dysfunction due to disturbances in brainstem function is of particular interest [11]. Clausen et al [53] and Mutch et al [54] have mentioned reduced carbon dioxide sensitivity and a lack of ability to increase ventilation during physical activity in patients with PPCSs. Reduced sensitivity to carbon dioxide results in abnormally high CBF during physical activity and may explain the exercise intolerance seen in many patients with PPCSs [53]. The findings by Clausen et al [53] underscore the importance of investigating brain physiology in this population. In this study, we have chosen a brain “stress” test consisting of a hypoxic challenge. This setup provides details regarding brain oxygen consumption, cerebrovascular reactivity, and the brain’s ability to increase glycolysis, which can manifest as an increase in brain lactate during hypoxia. The responses in young healthy individuals include maintained oxygen consumption, a pronounced increase in brain blood flow, and lactate production [30,33]. In older people, the ability to increase brain blood flow is diminished, and this results in a small but significant decrease in oxygen consumption [32]. Patients with sleep apnea show a reduced CBF response to hypoxia, and continuous positive airway pressure treatment has been found to normalize this pattern [29]. Patients with type 1 diabetes show a normal CBF response to hypoxia but significantly reduced lactate production during hypoxia, indicating impaired glycolytic activity [55]. In patients with multiple sclerosis (MS), the expected increase in blood flow is reduced, and a pronounced fall in oxygen consumption occurs ([name], unpublished data, May 2026). In this study on MS, vascular reactivity to carbon dioxide was tested and found to be normal. Hypercapnia and hypoxia induce cerebral vasodilation through different mechanisms [56]. In hypercapnia, carbon dioxide lowers local pH, which opens K^+^ channels in vascular smooth muscle cells, reduces Ca²^+^ influx, and thereby promotes vasodilation. Hypoxia induces vasodilation through a complex process that likely involves multiple mechanisms. Hypoxia stimulates nitric oxide release from nitric oxide synthase in both endothelium cells and neurons. Nitric oxide activates several enzymatic pathways, ultimately resulting in vasodilation and CBF increase. Thus, the hypoxic brain “stress” test investigates fundamental elements of brain physiology. The cerebrovascular response to hypoxia has not been systematically investigated in patients with PPCSs. The motivation to study BBB integrity is based on previous findings of increased BBB leakiness in both experimental mTBI animal models and patients with mTBI and PPCSs [15,57-60]. The BBB is important for maintaining proper brain function and a precise biochemical brain tissue environment while serving as a barrier against the entrance of toxic molecules, bacteria, and viruses. The function of the BBB is also highly related to vascular reactivity. In this study, we have used DCE MRI, which is a highly sensitive method that has been used previously for the detection of subtle leakiness in patients with MS [61-63].

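### In the baseline patient-versus-healthy hypoxia model, age and sex adjust the CMRO2 level but not the saturation slope that β3 tests

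*Protocol article*

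**What the plan says.** The first hypoxia model under Statistical Analysis in the protocol article applies to baseline data. Its outcome "denotes CMRO2, Group refers to either healthy controls or patients with PPCSs". The terms are group, measured SaO2, their product (β3), age, sex and a random intercept per participant. The article reads β3 as informing on the patient's "ability to maintain CMRO2 under hypoxic stress conditions". Age and sex each appear once, as main effects; neither is crossed with SaO2.

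Four other places bear on this model:

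- Objectives, Subproject 3: patients are to be "compared with a group of healthy age-matched controls". Age is the only matching variable named.
- Eligibility Criteria: patients may be 18 to 70 years old.
- Randomization and Blinding: the article notes that "PPCSs are more prevalent among women than men".
- Discussion: "In older people, the ability to increase brain blood flow is diminished, and this results in a small but significant decrease in oxygen consumption". The limitations paragraph adds that failing to complete all four MRI sessions was accepted.

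**The concern.** The comparison of patients with healthy controls is not randomized, so only matching and covariate adjustment protect it. The authors evidently mean to adjust for age and sex, since both are in the model. But the quantity tested is a slope, and the adjustment acts on the level. By the article's own account, age changes the slope: a fall in oxygen consumption under hypoxia in older people is an age effect on the relation between CMRO2 and saturation.

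If the patients with usable hypoxia scans are on average older than the controls, part of this age effect would appear as a concussion effect. If they are younger, it could mask a real one. The contrast carries one of the hypotheses of Subproject 3, and a planned paper concerns reduced cerebral oxygen metabolism in these patients.

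**Working it through.** The article gives no effect size, variance or sample size for this contrast, so there is no stated figure to reproduce. The structural point needs none.

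**Why the main effects do not reach β3.** Take one participant measured in normoxia (saturation S1) and in hypoxia (S2). Subtracting the two model equations gives

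Y1 − Y2 = (β2 + β3·Group)·(S1 − S2) + error.

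The intercept, the group main effect, β4·Age, β5·Sex and the random intercept all cancel. β3 is estimated almost wholly from such within-person differences, so terms that are constant within a person can hardly change it.

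**What passes into β3.** Suppose the true SaO2 slope changes by g per year of age and by s for female sex. Then, approximately,

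bias in β3 = g × (mean age gap) + s × (difference in proportion of women).

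Both parts are zero when the groups are balanced.

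**Illustration.** Every input is an assumption: 70 patients, 35 controls, age SD 13 years, saturations near 98% and 80%, between-person SD 15, residual SD 6, g = 0.0125 CMRO2 units per saturation point per year, no true group effect, 200 simulated trials per cell. Cells show the mean estimate of β3, with rejection at nominal 5% in brackets.

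| Scenario | Formula | Model as written | With Age×SaO2 and Sex×SaO2 |
|---|---|---|---|
| Age and sex balanced | 0 | 0.00 (7%) | 0.00 (8.5%) |
| Patients 5 years older | 0.0125 × 5 = 0.0625 | 0.07 (10.5%) | 0.01 (4%) |
| Patients 10 years older | 0.0125 × 10 = 0.125 | 0.13 (25.5%) | 0.00 (3.5%) |
| 75% v 50% women, s = 0.3 | 0.3 × 0.25 = 0.075 | 0.06 (11%) | 0.00 (4%) |
| 75% v 50% women, s = 0 | 0 | 0.01 (5%) | −0.01 (4.5%) |

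The Monte Carlo error of the rejection rates is about 1.5 to 3 points. The balanced row is therefore noisy, but neither model shows bias there.

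Over an 18-point desaturation, the 5-year and 10-year biases amount to 0.0625 × 18 = 1.1 and 0.125 × 18 = 2.25 CMRO2 units.

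**A steeper assumption, for range.** With g = 0.03 per year, 60 patients, 30 controls and residual SD 8 (150 runs), the model as written gave:

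- a 5-year gap: mean β3 of 0.13, rejection 19%;
- 75% v 50% women with s = 0.5: mean β3 of 0.12, rejection 15%;
- both together: mean β3 of 0.26, rejection 35%.

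The added terms brought rejection back to 4–8%. But this g implies 0.03 × 40 × 18 = 21.6 units between ages 25 and 65, more than the assumed between-person SD of 15. That fits poorly with an age effect the article calls small. The milder g implies 0.0125 × 40 × 18 = 9 units.

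**The case against.** The strongest reply is that age is dealt with by design. It is the matching variable, and if matching holds, the missing Age×SaO2 term causes no appreciable bias however wide the age range. The 5-year and 10-year scenarios assume that balance fails. This stands as a limit on the likely size. It does not make the term needless: matching is described in one phrase, and incomplete scanning was accepted, so those analysed may not have the balance of those recruited.

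On sex, no passage says that it alters the hypoxic response, and the controls' sex mix is not given. An article's silence does not show that sex was left unmatched. The sex part therefore remains conditional.

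A reader might go further and infer that eligibility admits patients with type 1 diabetes, sleep apnea or multiple sclerosis, whose altered hypoxic response would be read as concussion. The documents do not establish this. The exclusion of conditions that can obscure postconcussion symptoms, applied at a doctor-led screening, may already remove some or all of them. Nor do the Discussion's statements all concern CMRO2. For type 1 diabetes it says: "Patients with type 1 diabetes show a normal CBF response to hypoxia but significantly reduced lactate production during hypoxia". For sleep apnea: "Patients with sleep apnea show a reduced CBF response to hypoxia". Only multiple sclerosis is tied to a fall in oxygen consumption. The brain lactate outcome under Secondary Outcomes is framed by training-group or control-group allocation, not against healthy controls.

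A reader might also carry the point over to the 12-week hypoxia model. That model compares randomized groups of patients, so this source of confounding does not apply.

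**Conclusion.** The point holds for one model: the baseline CMRO2 hypoxia comparison of patients with healthy controls. There, the age and sex adjustment does not act on the coefficient being tested, and the article itself supplies the reason to expect an age effect on that coefficient.

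The size of any bias is unknown from the document. It is about zero if those with usable hypoxia scans are balanced on age and sex, and otherwise grows in proportion to the imbalance. The rejection rates above rest wholly on assumed inputs and show only what moderate imbalance could do. The sex component needs the further assumption that sex changes the response.

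The primary outcome, the randomized 12-week comparison and the lactate outcome by allocated group are untouched. This is a cheap improvement to a secondary, non-randomized analysis, not a threat to the trial's main result.

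**What to change.** Add Age×SaO2 and Sex×SaO2 to the baseline CMRO2 hypoxia model, keeping the existing main effects. Centre age, so that the SaO2 main effect remains interpretable; centring does not change β3. The coefficient then compares patients with controls of the same age and sex, which is what the adjustment appears intended to achieve.

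The cost is two degrees of freedom and a slightly wider interval for β3 when the groups are already balanced. Age and sex are already covariates in the plan, so no new data are needed. The article describes analysis as still under way, so the change can be recorded before this model is reported.

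Optionally, a sensitivity analysis can leave out any patient whose existing screening record shows type 1 diabetes, sleep apnea or multiple sclerosis. The two added terms would not correct for such a condition. Table 1 lists no separate comorbidity item, so this is possible only if the records hold the information.

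### The 12-week CMRO2 model has a three-way interaction but none of its two-way terms, so β4 measures mainly a shift in CMRO2 level and not the hypoxic response

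*Protocol article*

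**What the plan says.** In the protocol article, Statistical Analysis, the question after 12 weeks is a change in how CMRO2 responds to desaturation: "only patients will be tested for a possible change in their ability to maintain CMRO2 during the hypoxic exposure". The article continues: "Patients will be split according to group allocation (CG or TG), and the model is formulated as follows". In plain notation the printed model is

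CMRO2 = β0 + β1 Group + β2 SaO2 + β3 Time + β4 (Group × SaO2 × Time) + β5 Age + β6 Sex + u_i,

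with one random intercept per patient. On the scale of the covariate it says that "SaO2 is the actual oxygen saturation level in blood measured during the experiment (ie, during normoxia and hypoxia"; no centring is mentioned. β4 is then interpreted: "The interaction term infers information on whether time (pre- or postintervention) has any impact on the group-specific CMRO2 response".

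The two neighbouring models are complete. The primary BCBT model has Group, Time and Group×Time. The baseline CMRO2 model has Group, SaO2 and Group×SaO2, and its interaction is given the matching reading: "The regression value *β*_3_ of the interaction term provides an inference regarding the patient’s ability to maintain CMRO2 under hypoxic stress conditions". Only the 12-week CMRO2 model omits lower-order terms.

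**The concern.** The ability to maintain CMRO2 in hypoxia is the slope of CMRO2 on SaO2. The treatment effect on that slope is the three-way coefficient, but only when the two-way terms are also in the model. Without Group×Time, a training effect that moves CMRO2 equally in normoxia and hypoxia has nowhere to go except β4. Without Group×SaO2 and SaO2×Time, a group difference in slope already present at baseline, or a slope change common to both arms, can also leak into it.

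A level shift is a realistic scenario here. Subproject 3 (Objectives) expects disturbed brain metabolism in patients and expects exercise to normalise it. This is also the only randomised CMRO2 model printed, and the Results section plans a separate RCT paper on brain oxygen metabolism. As written, the analysis could report a changed hypoxic response where none exists, or report a real one in the wrong direction.

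**Working it through.** The documents give no figure for this analysis to reproduce, so the check is algebra on the printed model followed by simulation.

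**Inputs.** From the article: 70 randomised 1:1 and a tentative 30% dropout (Sample Size Calculation), so 35 × 0.7 = 24.5, taken as 24 per arm; two visits, each with normoxia and hypoxia; hypoxic air with 12%–14% oxygen (MRI Protocol). Assumed, because the article does not give them: SaO2 about 98% in normoxia and 80% in hypoxia, the CMRO2 variances (in µmol/min/100 g), and 0/1 coding of Group and Time.

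**Step 1: what the product column is.** With 0/1 coding, Group×SaO2×Time is zero except in the training group after the intervention, where it equals SaO2. Write SaO2 = 89 + d with d = ±9. The product is then 89·(Group×Time) + (Group×Time)·d, a level part plus a slope part. A quarter of the rows have Group×Time = 1.

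- Variance of the level part: 89² × (1/4)(3/4) = 1485.2
- Variance of the slope part: 81 × 1/4 = 20.25
- Correlation of the product with Group×Time: √(1485.2/1505.4) = 0.993
- Correlation with the slope part: √(20.25/1505.4) = 0.12

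One simulated data set in which saturation also varied between patients gave 0.994 and 0.17. No CMRO2 variance enters this step.

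**Step 2: simulation, patient SD 18, residual SD 10, REML, SaO2 in percentage points.** Ranges cover repeat runs.

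| Truth | Printed model | Complete model |
|---|---|---|
| Level shift 5, no slope change | β4 significant in 38–42% | 4–7% |
| Level shift 7.5, no slope change | 72% | 4–7% |
| Level shift 10, no slope change | 91–92% | 4–7% |
| Slope change +0.8, normoxia unchanged | mean β4 −0.05; 30–31% significant | mean +0.79 to +0.81; 71% |

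Smaller level shifts of 2 and 3 units give 10% and 18% with the printed model.

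**Step 3: why the sign turns.** Keep the true slope change at +0.8 and move only the saturation at which CMRO2 is unchanged:

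| CMRO2 unchanged at SaO2 of | Mean CMRO2 shift over 98 and 80 | Mean β4, printed model |
|---|---|---|
| 98 | 0.8 × (89 − 98) = −7.2 | −0.053 |
| 89 | 0 | +0.026 |
| 80 | 0.8 × (89 − 80) = +7.2 | +0.103 |

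The slope itself contributes +0.026, which is 0.026/0.8 = 3% of its true value. The rest, about ±0.08, is close to the average shift divided by mean saturation (7.2/89 = 0.081). The level part decides the sign.

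**Step 4: second set of assumptions.** SaO2 as a fraction (0.98, SD 0.01; 0.80, SD 0.04), patient SD 20, residual SD 10, known variance components, 600 runs.

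| Truth | Printed model | Complete model |
|---|---|---|
| No effect | 5.2% | 4.8% |
| Level shift +10 | mean β4 10.7; 91.0% | 5.2% |
| Slope change −100, unchanged at mid-range | mean −3.1; 15.0% | mean −99.3; 89.8% |
| Slope change −100, normoxia unchanged, hypoxic CMRO2 +18 | mean +6.9; 58.2% | mean −97.9; 88.0% |

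In the last row hypoxic CMRO2 is better maintained, yet the printed model points to a steeper fall. With ±0.5 coding and raw SaO2 the picture is the same: 91.7% for the level shift and 5.7% for the mid-range slope change.

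**Step 5: visit error.** With no effect at all, a visit-level SD of 5 raised the printed model's rejection rate to about 6–8%, and an SD of 10 to about 12–17%. These SDs are assumed.

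**The case against.** **The product may be shorthand for a full factorial, or SaO2 may be centred in practice.** The text does not support the first reading: main effects are listed separately, the product has one coefficient, and the neighbouring models write out every term. Centring is not stated, and it is not enough by itself. With centred SaO2 and 0/1 coding, a slope difference of 60 per unit SaO2 that is present only between groups, or only over time in both arms, gives a mean β4 of about 40 and about 62% rejection, against 3–4% in the complete model. Only centring combined with ±0.5 coding avoids the problem without the two-way terms.

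**The wrong sign depends on the scenario.** This stands. In Step 3 the sign is wrong only when normoxic CMRO2 is unchanged. That is, however, the natural picture of an effect confined to hypoxia.

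**The visit effect is a lesser point.** This also stands. The inflation in Step 5 arises because β4 behaves as a between-visit contrast. In the complete model without a visit term, the three-way test is conservative (3.1% and 1.1% at visit SDs of 5 and 10). There the visit intercept matters for power and for the Group×Time test.

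**The outcome is secondary, and further tests are called hypothesis-generating.** True, and the article says the baseline MRI tests will be repeated at 12 weeks with the intervention as a regressor, so a level shift may also be seen separately. But the hypothesis-generating statement concerns multiplicity. It does not make β4 measure what the article says it measures.

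**Conclusion.** The concern holds: the model is wrong as written. β4 cannot separate a training effect on the CMRO2 level from an effect on the hypoxic response, and with uncentred saturation it is almost entirely the former. The near-collinearity (0.99) follows from the printed equation whenever SaO2 is large relative to its spread. The rejection rates (about 40% to 92% for level shifts of 5 to 10 units, against about 5% for the complete model) depend on the assumed saturations, variances and effect sizes; with no training effect and no visit error the printed test keeps its 5% level. The sign reversal applies when the change is confined to hypoxia. The primary BCBT model contains its lower-order terms and is not affected, but the equation must be corrected before the randomised CMRO2 result is reported.

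**What to change.** Replace the printed equation with the hierarchically complete model: Group, Time, SaO2 centred at the normoxic value, Group×SaO2, Group×Time, SaO2×Time and Group×SaO2×Time, with age and sex as planned. Add a random intercept for visit within patient to the patient intercept. Read the effect on the hypoxic response from the three-way term and the effect on the resting CMRO2 level from Group×Time, and state both readings along with the coding of Group and Time.

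The cost is one model line in the analysis plan and code: three more fixed effects and one more variance component. No new data are needed. The article says analysis is still in progress, so the change can be made and documented before the results are reported.

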Structural equation modeling (SEM) and latent class analysis (LCA) will be used to identify latent variables and subgroups associated with PPCSs. Both approaches will be applied in an exploratory framework to generate hypotheses for future research. In the SEM analyses, observed variables will be treated as manifestations of an underlying normally distributed latent construct representing PPCS severity. The model will include the summed Rivermead score, time cycled and maximal workload during the BCBT, MRI-based CMRO2 measurements under normoxia and hypoxia, and BBB permeability. The latent variable will be scaled to the summed Rivermead score to facilitate interpretation. By integrating information across multiple domains, we aim to obtain a more comprehensive and sensitive representation of symptom severity than can be obtained with any single measure alone. Conceptually or procedurally related indicators (eg, fatigue-related items, BCBT variables, and MRI measures) will be modeled to account for residual correlations by including terms describing local dependence. This is performed to avoid inflating latent factor loadings or identifying spurious subgroups driven by unmodeled shared variance. In the LCA analyses, observed variables will be treated as indicators of an underlying categorical latent variable. Patients will thus be grouped according to their multivariate response profiles. The number of classes will be estimated using information criteria (Akaike information criterion and Bayesian information criterion) and by excluding solutions with very small or clinically uninterpretable classes. Given the limited sample size, we will restrict models to a maximum of four classes. For each class, we will estimate the expected response pattern and assess whether the resulting classes have meaningful clinical interpretations. Associations between latent outcomes and external covariates, such as age and sex, will be examined post hoc, with covariates treated as external variables rather than incorporated directly into the latent variable models. This includes assessing whether patients are exercise-intolerant, defined by both clinical criteria and self-reported experience. Finally, we will extend the models to incorporate both baseline and follow-up data. In the SEM analyses, we will estimate the effect of the intervention on the latent PPCS construct, while in the LCA analyses, we will test whether the intervention effect differs across latent classes.

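### The number of latent classes is chosen only among class models, with no deciding criterion named and no comparison with the severity continuum that the SEM assumes

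*Protocol article*

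**What the plan says.** All of this stands in the protocol article, Methods, Statistical Analysis, in the paragraph on SEM and LCA.

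- **Continuum model.** In the SEM, "observed variables will be treated as manifestations of an underlying normally distributed latent construct representing PPCS severity". Its indicators are listed: "The model will include the summed Rivermead score, time cycled and maximal workload during the BCBT, MRI-based CMRO2 measurements under normoxia and hypoxia, and BBB" (the last being how leaky the barrier is).
- **Class model.** In the LCA, "observed variables will be treated as indicators of an underlying categorical latent variable". No separate indicator list is given for it.
- **Selection rule.** "The number of classes will be estimated using information criteria (Akaike information criterion and Bayesian information criterion". A filter works alongside these criteria, since the choice is also made "by excluding solutions with very small or clinically uninterpretable classes". The ceiling is explicit: "Given the limited sample size, we will restrict models to a maximum of four classes".
- **Safeguard.** Related indicators get local-dependence terms: "This is performed to avoid inflating latent factor loadings or identifying spurious subgroups driven by unmodeled shared variance".
- **Status and use.** "Both approaches will be applied in an exploratory framework to generate hypotheses for future research". The classes are nevertheless carried into a test of whether the intervention effect differs between them, and the Results section plans a separate publication on the SEM and latent-group work.

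The paragraph does not say which criterion prevails when AIC and BIC disagree. It also describes no comparison between the selected class solution and the one-factor model.

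**The concern.** The rule ranks class solutions only against each other. A one-class result is allowed, but one class with dependence confined to related blocks means that symptom score, bike-test performance and MRI measures are unrelated across domains. That is not a severity continuum. If the SEM's own assumption is true, no candidate open to the LCA is right. A solution that cuts the continuum into mild and severe slices can then fit better than one class, simply because it reproduces the correlation between domains.

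The result at stake is the subgroup finding itself. Slices of a continuum would be described as patient types and then used in the class-by-intervention test. The unnamed tie-break also matters, because AIC and BIC penalise an extra class very differently at this sample size.

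**Working it through.** The plan states no error rate for this rule, so there is no figure of its own to reproduce. The check is a parameter count followed by a simulation.

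**Inputs from the article:** 70 patients randomised; 30% tentative dropout, so 70 × 0.7 = 49 as a lower case; the six SEM indicators; at most four classes; local-dependence terms within related indicators.

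**Assumptions (not in the article):** the LCA uses the same six indicators, treated as Gaussian; class covariances are equal; a class under 10% counts as very small; factor loadings are 0.3, 0.5 or 0.7; residual correlation is 0.6 within the bike-test pair and within the CMRO2 pair, and 0.2 between each CMRO2 measure and BBB permeability. A common loading λ implies a cross-domain correlation of λ², that is 0.09, 0.25 and 0.49.

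**Step 1: penalties.** AIC = −2 log L + 2p and BIC = −2 log L + p ln n.

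- One class: 6 means + 6 variances + 4 within-block covariances = 16 parameters.
- Each further class adds 6 means + 1 proportion = 7, so two classes need 23 and four need 37.
- The one-factor model adds 6 loadings to the 16, giving 22, one fewer than two classes.
- With ln 70 = 4.25, going from one class to two must raise 2 log L by more than 7 × 2 = 14 under AIC, but by more than 7 × 4.25 = 29.7 under BIC.

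**Step 2: the rule as written, no true classes.** Data came from one normal severity factor, with 150 data sets per cell (standard error at most √(0.25/150) = 4 percentage points). Entries are the share of data sets in which two or more classes were chosen, local-dependence terms included.

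| Loading | AIC, n=70 | BIC, n=70 | AIC, n=49 | BIC, n=49 |
|---|---|---|---|---|
| 0.3 | 65% | 1% | 68% | 3% |
| 0.5 | 93% | 29% | 87% | 23% |
| 0.7 | 99% | 99% | 100% | 92% |

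A second simulation at n=70, also with local-dependence terms and classes under 10% dropped, gave 54/74/94/100% for AIC and 0/3/29/100% for BIC at loadings 0/0.3/0.5/0.7. At loading 0.5 the two criteria differ by 93 − 29 = 64 points in the table, so the unnamed tie-break largely settles the answer there. Requiring both to agree gave the BIC rates.

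**Step 3: sensitivity.**

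- Without local-dependence terms: AIC 98–100%, BIC 82–100%.
- Class-varying covariances, with local dependence, n=70, loadings 0.5/0.7: AIC 85/97%, BIC 1/31%.
- No residual correlation in the data, local dependence modelled, n=70, loadings 0.5/0.7: BIC 51/99%.
- Categorical LCA on 16 Rivermead-like items: AIC 59–100%; BIC 0–1% at 0.3, 45–95% at 0.5, 100% at 0.7.

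**Step 4: one-factor model added as a competitor.** Same data as the table, loadings 0.3/0.5/0.7.

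- BIC: 1/11/3% at n=70 and 3/12/6% at n=49. The second simulation gave 0/0/10/1% at loadings 0/0.3/0.5/0.7 (n=70).
- AIC: 60/59/25% at n=70 and 63/65/26% at n=49. The comparator alone does not cure AIC.

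**Step 5: cost when classes are real.** With a true two-class structure at n=70, the BIC comparison kept the classes in 99% of runs at loading 0.7 and 100% at 0.85.

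**The case against.** The strongest reply is that the article already guards against spurious subgroups. It prescribes local-dependence terms, discards tiny or clinically meaningless classes, allows one class, caps the number and labels the work hypothesis-generating. An SEM and an LCA on the same domains are two exploratory views, not a contradiction. A comparator model could also sit in an analysis plan that is not shown.

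Much of this stands. The local-dependence terms help greatly: BIC at loading 0.3 and n=70 falls from 94% without them to 1% with them. However, the table already includes those terms and a class-size filter, and the problem remains for AIC throughout and for BIC at high loadings. The interpretability screen could not be simulated. It is unlikely to remove mild and severe slices, because they look interpretable. As to the missing plan, the article does not leave class selection open: it states the criteria, the ceiling and the exclusions, and the rule so stated is the one examined here.

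A reader might infer that the rule will usually report subgroups where none exist. The documents do not support that. It is true of AIC under these assumptions. It is not true of BIC at low to moderate loadings, and the article neither makes AIC decisive nor gives any loadings. A loading of 0.7 would require a correlation of 0.49 between, for example, Rivermead score and BBB permeability, and nothing in the article speaks to that.

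A reader might also want a tighter ceiling than four classes. Nothing here supports one: the improvement in Step 4 came from BIC with the comparator, and a lower ceiling could hide a real structure. The power of the class-by-intervention test is a separate question that does not bear on the selection rule.

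**Conclusion.** The point holds in limited form. The stated rule cannot distinguish subgroups from a severity continuum, and it leaves open which of two sharply different criteria decides. The size of the risk depends on loadings that the article does not give. If BIC decides, it runs from negligible at weak loadings to near certainty at strong ones with equal class covariances, and to 31% with class-varying covariances. If AIC decides, spurious classes were chosen in the majority of data sets in every continuum scenario tried.

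These figures rest on the assumption that the LCA shares the SEM's six indicators and on the assumed 10% class-size cut-off. The matter is minor: it concerns an exploratory analysis, and neither the primary model nor the planned MRI regressions are touched.

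**What to change.** Three changes of wording in the analysis plan, settled before class results are seen:

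1. Name BIC as the criterion that decides the number of classes.
2. Fit the one-factor model, with the same residual covariances, to the same indicators and patients as the LCA, and include it in the BIC comparison.
3. Report subgroups, or present the class-by-intervention test as evidence about subgroups, only if a class solution beats both the one-class and the one-factor model. Otherwise report that the data are consistent with a severity continuum.

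The ceiling of four, the local-dependence terms and the class filter can stay. If the full analysis plan already contains such a comparison, only the article's description needs aligning.

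The cost is small, since a one-factor severity model is already to be fitted. The downside is that the exploratory paper may have to report no subgroups.
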